### **Objectives, Specific Aims and Rationale**

- Primary aim: To examine if atopic eczema is associated with increased risk of all cancers and a number of specific cancers.
- Secondary aim: To examine if the risk depends on severity and activity of eczema, age, sex, coexisting asthma and systemic immunosuppressive treatments.

Of note, the study will also be conducted by colleagues in the United Kingdom in parallel.

**Study Design:** Nationwide matched cohort study.

### **Data sources**

- The Danish National Patient Registry (inpatients since 1977, outpatient/emergency rooms since 1995)
- The Danish Cancer Registry (since 1943)
- The Civil Registration System (since 1968)
- The Danish National Health Service Registry (since 1990)
- The Danish National Prescription Registry (since 1995)
- Socioeconomic data (educational data since 1981, income and partnership data since 1980)

### **Study Population**

The study will include an exposed cohort of persons with eczema and a comparison cohort including matched persons from the general population. The Danish Health Data Authority has already sampled the eczema exposed and unexposed cohorts described below.

Note: A sibling cohort has also been sampled by the Danish Health Data Authority, but is not included in this analysis plan, as we do not expect to include it in the current study.

## Analysis plan

### *Eczema exposed*

- Persons with a diagnosis of atopic eczema (ICD-8: 691; ICD-10: DL20) in the Danish National Patient Registry between 1 Jan 1977 and 10 February 2018.
- We include all primary and secondary diagnoses for eczema from admissions, hospital outpatient clinics and emergency rooms in the Danish National Patient Registry, including ongoing contacts (that is, persons who at the end of study period are in active follow-up in a hospital outpatient clinic).
- Index date = The earliest hospital record for atopic eczema (date of admission or first outpatient appointment).
- Only persons who are born in Denmark and living in Denmark on the index date (i.e. date of first record for eczema).

For the current study, we will further restrict the study population as follows:

- We will exclude eczema patients (together with their matched comparators) identified by an ICD-8 diagnosis recorded together with an additional (“modification”) code indicating that it potentially an uncertain/unverified/working diagnosis (c\_diagmod=1–7).
- We will exclude patients (together with their matched comparators) with inconsistencies in registration of status and residence in the Civil Registration System (recorded as alive but not living in Denmark but without an emigration date), as we assume that these patients are not living in Denmark and thus not eligible.
- To ensure that we have at least 1 year of registration history from included registries (except the prescription registry), we will only include patients (together with their matched comparators) with index date on 1 January 1982 or later. In the subanalysis on severity and in a sensitivity analysis, we restrict to those diagnosed on 1 January 1996 or later in order to ensure one year of registration history in all databases.
- To ensure at least 1 year of follow-up after start of eligible follow-up (available until 30 June 2017), we will include eczema patients until 30 June 2016.
- We will exclude eczema patients (together with their matched comparators) with a record for any cancer (except non-melanoma skin cancer) before or on index date (see Table 2). That is, we will not only exclude those with history of the cancer outcome of interest. However, in analyses of non-melanoma skin cancer specifically, we will exclude those with previous history of this cancer as well.

### *Unexposed cohort*

- Up to 10 persons matched to each eczema patient by sex and birth year.
- Comparators have to: (1) be born in Denmark, (2) be alive and living in Denmark on the on index date of their matched eczema-exposed individual (i.e. first hospital eczema diagnosis), and (3) have no previous diagnosis of eczema.
- Index date = The same index date as their matched eczema-exposed individual

As with eczema patients, we will additionally apply the following restrictions:

- We will exclude matched comparators with inconsistencies in registration of status and residence in the Civil Registration System (recorded as alive but not living in Denmark but without an emigration date), as we assume that these patients are not living in Denmark and thus not eligible.
- We will exclude comparators with any cancer (except non-melanoma skin cancer) before or on index date (see Table 2). That is, we will not only exclude those with history of the cancer outcome of interest. However, in analyses of non-melanoma skin cancer specifically, we will exclude those with previous history of this cancer as well.

### *Exposure subgroups*

For the secondary aim, we will identify severe and active eczema. The analyses will be performed if feasible in terms of sample size.

We will categorize severity as moderate or severe. Severe eczema will be defined as (1) either phototherapy or systemic treatment for eczema (cyclosporine, azathioprine, mycophenolate, methotrexate, dupilumab), identified in Patient Registry (procedure codes: “BNGA1” “BNGA2” “BNGA3” “BNGA4” “BOHJ18B8” “BWHB83” “BWHA115” “BOHJ20” “BOHJ22”) or Prescription Registry (ATC codes: “L04AX01” “L01BA01” “L04AX03” “L04AD01” “L04AA06” “D11AH05”) or (2) admission to hospital with eczema as the primary reason for admission (i.e. where eczema is recorded in the primary diagnostic position for an in-hospital contact). Severity will be included as a time-updated variable. Thus, a patient with eczema will be classified as having moderate eczema from index date (unless they develop severe eczema). When (and if) a person fulfills the definition for severe eczema, we will classify them as having severe eczema from the

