## Analysis plan

point at which they meet the definition for ‘severe eczema’. Once a person fulfills the criteria for severe disease, he/she will remain in that category for the rest of follow-up. At any given point during follow-up, atopic eczema patients will therefore belong to one of two severity categories: moderate or severe.

We will classify activity of eczema based on consultation and treatment patterns within the first year after index date, as illustrated in the Figure below. A person will be considered to have active eczema that lasts 3 months from either 1) a consultation to a private-practicing dermatologist (any consultations coded with specialty ‘04’ in The Danish National Health Service Registry), 2) a primary care prescription for eczema therapies (Prescription Registry ATC codes: “D07” “D11AH01” “D11AH02” “L04AX01” “L04AX03” “L04AD01” “L04AA06” “H02AB” [excluding injections] or Patient Registry procedure codes: “BNGA1” “BNGA2” “BNGA3” “BNGA4” “BOHJ18B8” “BWHB83” “BWAH115” “BOHJ20” “BOHJ22”) or 3) a hospital record for eczema. Each time a person fulfills one of these criteria, the active period will be extended by 3 months from that date. We will then compute the percentage of time with active eczema in the first 12 months after index date as the number of months with active eczema divided by 12 months. We will then classify persons as: 0=unexposed; 1=those who never had active atopic eczema in the first year; 2=those who had active atopic eczema for less than 50% of the first year; 3=those who had active atopic eczema for at least 50% of the first year. In order to classify activity, follow-up will start at 12 months after index date in activity analyses. Note that periods of disease activity will be identified irrespective of the classification for disease severity.

**Figure.** Illustration of active eczema disease

[figure not shown]

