|                                                                                                    |                  | "DC94" "DC95"
"DC81" "DC82"
"DC83" "DC84"
"DC85" "DC86"
"DC88" "DC96"           |                                        |
| Use of oral corticosteroids                                                                        |                  | "H02AB" and
DOSFOR M "TAB"
or
"TABMO D"                                            | Any prescription excluding injections. |
| Systemic treatment for eczema (cyclosporine, azathioprine, mycophenolate, methotrexate, dupilumab) | Procedure codes: | "L04AX0 1"
"BOHJ18 B8"
"BWHB83 3"
"BWAH1 15"
"BOHJ20"
"BOHJ22"
"D11AH0 5" |                                        |
| Asthma                                                                                             | "493"            | "DJ45" "DJ46"                                                                               |                                        |

Note: All subcodes are included unless otherwise stated; all types of contacts (inpatient, outpatient and emergency) and both primary and secondary diagnoses should be considered. Use admission/prescription/record date for all variables.

aBaseline information only

bDocumentation is available here:

<https://www.dst.dk/da/Statistik/dokumentation/Times/forskningsservice/efalle>

<https://www.dst.dk/da/Statistik/dokumentation/Times/cpr-oplysninger/c-faelle-id>

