## Analysis plan

Cancer of the brain, hypophysis,  
corpus pineale and ductus  
craniopharyngealis

Unexposed

Exposed

Spinal cord, cranial nerve and  
other CNS tumours

Unexposed

Exposed

Estimated hazard ratios from Cox regression with time since index date as underlying timescale, stratified by matched set. Adjusted additionally for **systemic treatment for eczema**.

Unadjusted: No adjustment.

Mediation model: Adjusted additionally for time-varying lifestyle-related diseases and **systemic treatment for eczema**.

9. We will repeat the main analysis after starting follow-up at 3 years after index date to limit potential reverse causality. If we see a large change at 3 years, we will also repeat the main analysis by changing start of follow-up to 5 years after index date.

**Table 9. Number of events, accumulated person-time, and HRs for cancer associated with eczema, Denmark. Starting follow-up at 3 years after index date.**

|                          | N | events | P-Y
at
risk | Rate
per
1,000 | Hazard ratio and 99%
confidence interval  |                    |
|--------------------------|---|--------|-------------------|----------------------|----------------------------------------------------------|--------------------|
|                          |   |        |                   |                      | Unadjusted                                               | Mediation
model |
| Any cancer               |   |        |                   |                      |                                                          |                    |
| Unexposed                |   |        |                   |                      |                                                          |                    |
| Exposed                  |   |        |                   |                      |                                                          |                    |
| Lung cancer              |   |        |                   |                      |                                                          |                    |
| Unexposed                |   |        |                   |                      |                                                          |                    |
| Exposed                  |   |        |                   |                      |                                                          |                    |

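### Severe eczema starts on the qualifying date with no lag, and the only reverse-causality check does not reach the severity analysis

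*Protocol*

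**What the plan says.** Protocol, Exposure subgroups: "Severity will be included as a time-updated variable". Everyone with eczema starts as moderate unless and until the severe definition is met. The triggers are phototherapy, a listed systemic drug, or "admission to hospital with eczema as the primary reason for admission". On timing: "When (and if) a person fulfills the definition for severe eczema, we will classify them as having severe eczema from the", continuing after the page break, "point at which they meet the definition for" severe eczema. Then: "Once a person fulfills the criteria for severe disease, he/she will remain in that category for the rest of follow-up". No lag, induction period or washout follows the switch.

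The note under the covariable table adds a dating rule: "Use admission/prescription/record date for all variables". If it also governs severity, which is not stated, the severe state begins at admission and not at discharge.

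Follow-up starts at the index date and ends at the first cancer. Previous cancer is excluded up to the index date.

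Sensitivity analyses, item 9: "We will repeat the main analysis after starting follow-up at 3 years after index date to limit potential reverse causality". A 5-year version follows if the change at 3 years is large. Its table shell has only exposed and unexposed rows. Items 16 and 17 look at skin cancer ascertainment for eczema overall, not by severity or by time since the switch.

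**The concern.** Worsening skin disease that leads to admission, phototherapy or systemic treatment may partly reflect a cancer not yet diagnosed, or may bring the investigation that finds one. Either way the person moves to severe shortly before the cancer is registered, and the event is charged to severe eczema. Item 9 shows that the sponsor takes this threat seriously at the first hospital eczema contact. The same reasoning applies at the switch, but no analysis is planned there.

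The severity table (results Table 3) is the evidence on whether risk depends on severity. A cluster of cancers soon after the switch could produce or enlarge a gradient between moderate and severe that reads as dose-response. The main contrast of eczema against comparators does not use the switch and is not affected.

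**Working it through.** The document gives no event counts, severe person-time or power, so there is no plan figure to reproduce. The first two steps compare the text and the rest is illustration on assumed inputs.

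**1. Which cancers count as severe.** Follow-up ends at the first cancer, so one dated before the trigger counts as moderate. For one dated on the trigger day no rule is given; in the usual (start, stop] coding it would count as moderate. One dated after the trigger counts as severe, however soon. If the admission-date rule applies to severity, that includes a cancer dated later within the same admission.

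**2. Does item 9 reach this?** It repeats the main analysis only, so no severity row has a delayed-start version. Extending it to severity would not be enough, because its clock runs from the index date. If switch dates were uniform over F years of follow-up (assumed), the share falling more than 3 years after index is 1 − 3/F: 40%, 70%, 80% and 85% for F = 5, 10, 15 and 20. For people severe from index the two clocks coincide; their share is not known.

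**3. Severe versus unexposed.** Take a true hazard ratio of 1, a cancer rate ratio R during the first w years after the switch, mean severe time T years and a constant baseline rate. Then the apparent ratio is about 1 + (w/T)(R − 1). R, w and T are all assumptions.

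| T (years) | w (years) | R = 2 | R = 3 | R = 5 |
|---|---|---|---|---|
| 5 | 0.5 | 1.10 | 1.20 | 1.40 |
| 5 | 1 | 1.20 | 1.40 | 1.80 |
| 10 | 0.5 | 1.05 | 1.10 | 1.20 |
| 10 | 1 | 1.10 | 1.20 | 1.40 |
| 15 | 0.5 | 1.03 | 1.07 | 1.13 |
| 15 | 1 | 1.07 | 1.13 | 1.27 |

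With w = 0.25 included, the range is 1.02 to 1.80. In a middle case (T = 10, w = 0.5, R = 3) the ratio is 1 + 0.05 × 2 = 1.10. The share of severe events inside the window is wR/(wR + T − w) = 1.5/11 = 14%; over the whole grid it is 3% to 56%.

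**4. Severe versus moderate.** Moderate time starts at the index date, where an early excess is also plausible. With rate ratios R_s and R_m in the two early windows, the spurious gradient is [1 + (w/T_s)(R_s − 1)] / [1 + (w/T_m)(R_m − 1)]. With w = 1 and T_s = T_m = 10:

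- R_s = 3, R_m = 1: 1.20/1.00 = 1.20
- R_s = 3, R_m = 2: 1.20/1.10 = 1.09
- R_s = 3, R_m = 3: 1.20/1.20 = 1.00
- R_s = 2, R_m = 3: 1.10/1.20 = 0.92

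So step 3 does not measure the gradient. Only the difference between the two early excesses does, and the document gives nothing from which to estimate it.

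**5. Person-time set aside by a lag.** This is at most about w/T, since people with short severe time lose only what they have. For 12 months: 1/15 = 7%, 1/10 = 10%, 1/5 = 20%. For 3 years: 3/15 = 20%, 3/10 = 30%, 3/5 = 60%.

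**The case against.** Switching at the qualifying date is a legitimate definition: it avoids crediting time before severe disease as severe. Severity is a secondary aim, analysed if feasible and possibly for overall cancer only. With 99% intervals and 10 comparators per patient, a spurious severe-versus-unexposed ratio of 1.2 would exclude 1 with probability of about 3%, 17% or 58% for 20, 100 or 300 severe events. All of this stands, and it argues against redefining the main severity analysis. It does not remove the gap, because a gradient can be read from the point estimates whether or not an interval excludes 1.

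A reader might infer four stronger things that the document does not support:

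- *Every cancer found in the same episode counts as severe.* Only those dated after the trigger clearly do (step 1). The admission trigger also needs eczema as the primary diagnosis, so an admission with eczema coded secondarily switches nobody.
- *A protection given to the activity analysis was withheld from severity.* The 12-month delay there exists to classify activity, not to limit reverse causality.
- *The plan itself flags lymphoma.* Ascertainment is raised for skin cancer only, and item 9 names no cancer. Cutaneous lymphoma codes are removed from the any-cancer and lymphoma outcomes, which closes one obvious route.
- *The ratios in step 3 are the false severity gradient.* Step 4 shows that they are not.

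One could also say that an extra sensitivity run belongs in a separate statistical analysis plan. But this document already fixes the switch rule, the model, the table shells and the list of sensitivity analyses, so the omission lies within what it specifies.

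**Conclusion.** The gap is real but limited. Severe status begins on the qualifying date without a lag, and the reverse-causality check neither covers the severity table nor runs from the switch. Cancers diagnosed shortly afterwards count as severe and could inflate the severe hazard ratio relative to moderate. The amount, and even the direction of the net effect on the gradient, depends on how the early excess differs between the two states and cannot be derived from the document. The 1.02 to 1.80 range is for severe against unexposed only and rests entirely on assumed R, w and T. The point concerns a secondary analysis and is a cheap improvement, not a defect in the main result.

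**What to change.** Keep results Table 3 (severity) as planned. Add a pre-specified sensitivity version, at least for any cancer, with the same model columns, in which entry to severe takes effect 12 months after the qualifying date, and a second version at 3 years to match item 9. Leave out the person-time and events in the lag window, or show them separately where counts allow. They should not be returned to moderate, since that would move the early excess into the comparison state. State in one sentence how a cancer dated on the qualifying day is assigned.

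The cost is one more time split in the severity data set and less precise lagged estimates. A 12-month lag sets aside about 7% to 20% of severe person-time for mean severe times of 15 to 5 years. The 3-year version could take up to 20% to 60% on the same assumption. Given the rule of thumb against publishing outcomes with fewer than 20 events, both may be reportable only for any cancer and the commoner sites.

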## Analysis plan

point at which they meet the definition for ‘severe eczema’. Once a person fulfills the criteria for severe disease, he/she will remain in that category for the rest of follow-up. At any given point during follow-up, atopic eczema patients will therefore belong to one of two severity categories: moderate or severe.

We will classify activity of eczema based on consultation and treatment patterns within the first year after index date, as illustrated in the Figure below. A person will be considered to have active eczema that lasts 3 months from either 1) a consultation to a private-practicing dermatologist (any consultations coded with specialty ‘04’ in The Danish National Health Service Registry), 2) a primary care prescription for eczema therapies (Prescription Registry ATC codes: “D07” “D11AH01” “D11AH02” “L04AX01” “L04AX03” “L04AD01” “L04AA06” “H02AB” [excluding injections] or Patient Registry procedure codes: “BNGA1” “BNGA2” “BNGA3” “BNGA4” “BOHJ18B8” “BWHB83” “BWAH115” “BOHJ20” “BOHJ22”) or 3) a hospital record for eczema. Each time a person fulfills one of these criteria, the active period will be extended by 3 months from that date. We will then compute the percentage of time with active eczema in the first 12 months after index date as the number of months with active eczema divided by 12 months. We will then classify persons as: 0=unexposed; 1=those who never had active atopic eczema in the first year; 2=those who had active atopic eczema for less than 50% of the first year; 3=those who had active atopic eczema for at least 50% of the first year. In order to classify activity, follow-up will start at 12 months after index date in activity analyses. Note that periods of disease activity will be identified irrespective of the classification for disease severity.

**Figure.** Illustration of active eczema disease

[figure not shown]

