**Subgroup analyses**

Depending on power, subgroup analyses may only be performed for overall cancer.

6. We will explore whether the association between eczema and cancer differs by eczema severity or eczema disease activity by stratifying separately on disease severity (Table 4) and activity (Table 5). The severity and activity analyses will be restricted to those with index date on or after 1 January 1996 to ensure at least 1 year of prescription history. Furthermore, the follow-up will start at 12 months after index date in the activity analysis in order to allow categorization of activity.

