Unadjusted: Adjusted additionally for **immunosuppression**.

Mediation model: Adjusted additionally for time-varying lifestyle-related diseases **and immunosuppression**.

11. We will repeat the main analysis additionally adjusting for use of **oral corticosteroids**. We will define use as a time-updated never/ever variable. Thus, individuals classified as exposed if they ever have a prescription for an oral corticosteroid, with status changing at the first prescription for an oral corticosteroid.

---

**Table 11. Number of events, accumulated person-time, and HRs for cancer associated with eczema, Denmark. Adjusting additionally for oral glucocorticoids.**

---

| N | events | P-Y
at
risk | Rate
per
1,000 | Hazard ratio and 99%
confidence interval  |                    |
|---|--------|-------------------|----------------------|----------------------------------------------------------|--------------------|
|   |        |                   |                      | ‘Unadjusted’                                             | Mediation
model |

---

---

|                                  |
|----------------------------------|
| Any cancer                       |
| Unexposed                        |
| Exposed                          |
| Lung cancer                      |
| Unexposed                        |
| Exposed                          |
| Breast cancer                    |
| Unexposed                        |
| Exposed                          |
| Prostate cancer                  |
| Unexposed                        |
| Exposed                          |
| Melanoma skin cancer             |
| Unexposed                        |
| Exposed                          |
| Keratinocyte skin cancer         |
| Unexposed                        |
| Exposed                          |
| Lymphoma                         |
| Unexposed                        |
| Exposed                          |
| Multiple myeloma                 |
| Unexposed                        |
| Exposed                          |
| Leukemia                         |
| Unexposed                        |
| Exposed                          |
| Meningioma                       |
| Unexposed                        |
| Exposed                          |
| Cancer of the brain, hypophysis, |
| corpus pineale and ductus        |
| craniopharyngealis               |
| Unexposed                        |
| Exposed                          |

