| Any cancer |   |        |             |                |                                                       |                 |
| Unexposed  |   |        |             |                |                                                       |                 |
| Exposed    |   |        |             |                |                                                       |                 |

Estimated hazard ratios from Cox regression with time since index date as underlying timescale, stratified by matched set.

Unadjusted: No adjustment.

Mediation model: Adjusted additionally for time-varying lifestyle-related diseases.

17. Because of particular concerns about ascertainment bias for skin cancer, we will perform analyses using stage of melanoma at diagnosis as outcome (if feasible). Decreasing HR with increasing stage could suggest a shift with diagnosis at an earlier stage (as a proxy for ascertainment bias).

**Table 17. Number of events, accumulated person-time, and HRs for melanoma associated with eczema, Denmark. According to stage at diagnosis.**

|                          | N | events | P-Y at risk | Rate per 1,000 | Hazard ratio and 99% confidence interval  |                 |
|--------------------------|---|--------|-------------|----------------|-------------------------------------------------------|-----------------|
|                          |   |        |             |                | Unadjusted                                            | Mediation model |
| Localized stage melanoma |   |        |             |                |                                                       |                 |
| Unexposed                |   |        |             |                |                                                       |                 |
| Exposed                  |   |        |             |                |                                                       |                 |
| Regional stage melanoma  |   |        |             |                |                                                       |                 |
| Unexposed                |   |        |             |                |                                                       |                 |
| Exposed                  |   |        |             |                |                                                       |                 |

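### Two of the triggers for active eczema need no eczema indication, so the activity gradient may partly reflect skin surveillance and airway disease, and none of the planned bias checks is specified for the activity table

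*Protocol*

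**What the plan says.** Under Exposure subgroups, the protocol scores eczema activity over the first 12 months after the index date from three kinds of trigger:

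1. A private dermatologist contact: "any consultations coded with specialty ‘04’ in The Danish National Health Service Registry".
2. A listed therapy or procedure. The list includes topical preparations (D07, D11AH01, D11AH02), systemic agents, phototherapy and other procedure codes, and "H02AB” [excluding injections" as its corticosteroid entry.
3. A hospital contact: "3) a hospital record for eczema".

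At each trigger "the active period will be extended by 3 months from that date". The share of active time is computed "as the number of months with active eczema divided by 12 months", and the exposed are classed as never active, below 50%, or at least 50%. Follow-up in this analysis starts 12 months after the index date.

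Item 6 announces the analysis as "stratifying separately on disease severity (Table 4) and activity (Table 5"); the activity table itself is captioned Table 4. It has rows for any cancer and each specific cancer, and two columns: unadjusted, and a mediation model that adjusts for lifestyle-related diseases including COPD.

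Elsewhere the protocol recognises the issues involved. Item 17 begins "Because of particular concerns about ascertainment bias for skin cancer" and examines melanoma by stage. Item 16 removes skin cancer from the all-cancer outcome. Item 11 adjusts for oral corticosteroids as an ever/never variable, "status changing at the first prescription for an oral corticosteroid". Item 9 delays the start of follow-up to 3 years.

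**The concern.** Of the three kinds of trigger, only the hospital record is tied to an eczema diagnosis. A dermatologist visit for a mole check or sun damage counts as eczema activity, and so does a prednisolone course for asthma or COPD. People under skin surveillance may go on having skin cancers found, and people with airway disease may have more lung cancer. If these people gather in the higher activity classes, the hazard ratio can rise with activity even when eczema activity has no effect. The rows most exposed are those where a gradient would most readily be taken as evidence for eczema.

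The any-cancer row is not immune. It includes melanoma, and people with earlier non-melanoma skin cancer stay in that analysis, so their skin checks would also score as activity.

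**Working it through.** The protocol gives no event count, effect size or share of unrelated contacts, so there is no planned figure to reproduce. Two things can be checked: how easily an unrelated contact changes a person's class, and what ratio could follow under stated assumptions.

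**1. Moving between classes.** Inputs from Exposure subgroups: 3 months per trigger, a 12-month window, and a cut-off of 50% (6 months). Overlapping time is counted once and time is truncated at month 12.

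- One trigger by month 9: 3/12 = 25%, so never active becomes below 50%.
- Two triggers at least 3 months apart, the second by month 9: 6/12 = 50%, the top class.
- The text does not say whether the index hospital record is itself a trigger. If it is, one further trigger between months 3 and 9 gives 6/12 = 50%, and the never-active class is empty.

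Placing unrelated triggers at uniformly random times (100,000 simulated persons per setting) gives the share reaching the top class:

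| Unrelated triggers | Index record not counted | Index record counted |
|---|---|---|
| 1 | 0% | 50% |
| 2 | 25% | 81% |
| 3 | 59% | 94% |
| 4 | 81% | 98% |

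Two cells can be confirmed exactly. For two triggers without the index record, both must fall in months 0 to 9 and be at least 3 months apart: (9 − 3)²/12² = 36/144 = 25%. For one trigger with the index record: (9 − 3)/12 = 50%.

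Assume instead a mean rate of unrelated triggers per person-year and no genuine eczema care after the index date. The share reaching the top class is then:

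| Assumed rate | Index record not counted | Index record counted |
|---|---|---|
| 0.1 | 0.1% | 4.8% |
| 0.25 | 0.7% | 11.9% |
| 0.5 | 2.7% | 22.6% |
| 1.0 | 9.8% | 41.1% |

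**2. Possible effect on the ratio.** Let m be the share of the top class made up of people with unrelated contacts, r the corresponding share in the class it is compared with, and k their cancer rate relative to everyone else. With no effect of activity, the ratio is [1 + m(k − 1)] / [1 + r(k − 1)]. All three values are assumptions.

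- m = 0.10, r = 0.05, k = 2: 1.10/1.05 = 1.05.
- m = 0.30, r = 0.10, k = 3: 1.60/1.20 = 1.33.
- m = r: 1.00. If r exceeds m, the ratio falls below 1 (for k above 1).

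**3. Which safeguards reach the activity table.**

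- Items 9 and 11 repeat the main analysis, item 16 the all-cancer analysis, and item 17 concerns melanoma in exposed versus unexposed. None is specified by activity class.
- The mediation column includes COPD, but Table 3 (Covariables) identifies COPD by hospital diagnosis codes only. Asthma is not in that model; it is used only to stratify the eczema-versus-comparator contrast (Table 7).
- The 12-month start removes cancers found in year 1. It does not remove continuing surveillance or persisting airway disease.

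**The case against.** A reader might infer that the gradient reflects surveillance and airway disease rather than eczema, and that the activity aim will be answered wrongly. The document does not support that. Everyone classified has a hospital diagnosis of atopic eczema, and the triggers also include topical therapies, systemic agents, phototherapy and eczema hospital records. Activity is a mixture, and the share of unrelated contacts is not given.

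A reader might also infer that the plan contradicts itself by using oral corticosteroids both as an activity trigger and as a covariate. It does not: one drug can mark activity in one analysis and be adjusted for in another.

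Nor should a spurious hazard ratio of 1.10 to 1.60 be read off the formula. Those values follow from m = 0.10, k = 2 and m = 0.30, k = 3 only with r = 0. The middle class also holds people with unrelated contacts: if the index record is not counted, one such contact puts a person there. The unexposed are not screened for such contacts. A steady rise across classes is therefore not established.

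Other points against stand in part. COPD is adjusted for in one column, and the 12-month start excludes cancers diagnosed at the classifying visits. The analysis is secondary, depends on feasibility, and may be limited to overall cancer. These reduce the concern but do not remove it: no check of the activity definition is specified, and the any-cancer row remains open.

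**Conclusion.** The point holds in a limited form. Two triggers do not require an eczema indication, two well-spaced contacts of this kind reach the top class, and none of the planned checks in items 9, 11, 16 and 17 is specified for the activity table. A gradient there may partly reflect skin surveillance for melanoma and keratinocyte cancer, and airway disease for lung cancer. COPD adjustment deals with the second only in part.

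Neither the size nor the shape of the bias can be derived from the document. The figures of 1.05 and 1.33 illustrate assumed values of m, r and k, and the ratio is 1.00 when the shares are equal. This calls for a cheap improvement to a secondary analysis. It does not show that the broad definition is unusable.

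**What to change.** Keep the broad activity definition as primary and pre-specify one repeat of the activity table:

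- Remove specialty-04 visits and H02AB prescriptions from the triggers.
- Add asthma to the adjustment.
- Report at least any cancer under both definitions and, where event numbers allow, melanoma, keratinocyte and lung cancer.
- State in advance that an activity gradient will be interpreted as an effect of eczema only if it persists under the narrower definition.

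Counting a dermatologist visit only when a topical prescription follows would add little, because D07 and D11AH01/02 dispensings are already triggers in their own right.

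The cost is one extra derived variable from registries already held. Some truly active patients, seen without a new prescription or treated with oral corticosteroids alone, will fall into a lower class in the repeat. Two limits remain: D07 is also not restricted by indication, and asthma in Table 3 (Covariables) is hospital-coded, so that adjustment too is partial. The same edit should say whether the index hospital record counts as a trigger, since this decides whether the never-active class can contain anyone.
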